## Abstract

**Introduction:**

Despite effective treatment of leprosy via WHO-approved multi-drug therapy (MDT), patients still suffer from debilitating neuropathic sequelae, including peripheral neuropathic pain (PNP), and continue to develop intercurrent etiologies (such as diabetes), and progressive existing neuropathy over time. Strategies seeking to improve physiological and metabolic wellness, including those that reduce systemic inflammation and enhance immune responsiveness to neurotoxic factors may influence underlying neuropathic etiologies. A whole food plant-based diet (WFPBD) has been shown to be effective in the management of neuropathic pain due to diabetes, limiting severity and relevant symptomology. Diabetes remains a significant sequela of leprosy, as up to 50% of patients in reaction requiring corticosteroids, may develop a biochemical diabetes. As nutritional interventions may modulate both leprosy and diabetes, a specific exploration of these relationships remains relevant.

**Objectives:**

(1) To demonstrate the effect of a WFPBD lifestyle intervention, on neuropathic pain variables in leprosy; and (2) To contextualize the significance of diet in the treatment of chronic sequelae in leprosy by evaluating tolerability and side effect profile.

**Methods:**

A prospective, randomized, controlled, single-blind, multicentre interventional trial is described. Weekly one-hour dietary counseling sessions promoting a WFPBD emphasizing vegetables, fruits, whole-grains, nuts, and legumes, omitting animal products, and limiting fat intake over a six-month duration will be implemented. Participants will be 70 age and sex-matched individuals experiencing active or treated “cured” leprosy and PNP, randomized to either intervention or control groups. Primary outcome measures include efficacy via visual analog scale, subjective questionnaire and objective quantitative sensory testing, as well as safety, tolerability, and harms of a WFPBD on PNP in leprosy. This study will be initiated after Research Ethics Board (REB) approval at all participating sites, and in advance of study initiation, the trial will be registered at ClinicalTrials.gov.

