Lifestyle interventions have recently emerged as accessible and cost-effective strategies to reduce the burden and severity of neuropathic pain in diabetes. Strategies seeking to improve physiological and metabolic wellness, including those that reduce inflammation and enhance immune responsiveness to neurotoxic factors may influence underlying neuropathic etiologies. Nutrient supplementation has been instrumental in reducing host oxidative stress, strengthening the immune system, and mitigating potential adverse events in both leprosy and diabetes (11–15). Specifically, oral vitamin E and zinc supplementation may confer antioxidant effects, reducing daily analgesic requirements, and decreasing the incidence of leprosy symptoms overall (14, 16, 17). Likewise, studies assessing the use of oral vitamin D3 and omega-3 supplementation in diabetes have shown statistically significant improvements on subjective tests of neuropathy and pain, as well as objective tests of nerve health (11–15). Dietary interventions have also been specifically shown to reduce overall symptomology and improve the quality of life of individuals suffering from PNP due to diabetes (18–22). Many leprosy patients will develop impaired glucose tolerance due to genetic and lifestyle factors alone, and also due to the reliance on corticosteroids for control of inflammatory leprosy reactions (which can occur before, during, and after effective MDT). As patients experiencing leprosy often endure a biochemically induced diabetes, similar rationale may be applied. Prior to a final diagnosis of leprosy, patients are statistically significantly more likely to have diabetes (up to 14.2%) or pre-diabetes (up to 50%), when compared to healthy controls. Likewise, up to 65% of patients require corticosteroid treatment following reactions, resulting in steroid-induced hyperglycemia in up to 47% of individuals who were previously glucose tolerant (23–28). Additionally, given the high population prevalence of diabetes, lifestyle and genetic factors may predispose those with leprosy to diabetic neuropathy independent of corticosteroid use.

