### 2.3. Inclusion and exclusion criteria

Participants will be enrolled at the Tropical Disease Unit (TDU) in Toronto, Ontario, Canada, and one or more partner tropical medicine institutes, and will include patients experiencing active, or treated “cured” leprosy, as well as any degree of PNP. Inclusion into the trial requires: (1) clinically compatible leprosy based on the presence of thickened peripheral nerves (on physical exam, as well as ultrasound), and hypo- or anesthetic skin lesions; and/or (2) laboratory confirmed leprosy via positive slit skin smears and/or consistent histopathology and/or the presence of acid-fast bacilli on histopathology; and/or (3) a clinically compatible presence of neuropathy on physical exam including but not limited to glove and stocking paresthesia, abnormal touch perception sensations, and subjective pain (40–42) (Table 1). Sensory perception will be evaluated using 0.2–0.6 g Semmes-Weinstein monofilament, and the presence of 2/3 insensate sites will be considered “abnormal” (43). The use of objective QST as a standalone test for inclusion will be dependent on enrolment frequency to better preserve trial specificity. In the event of inadequate enrolment, a negative QST will not exclude patients from the trial to ensure adequate sensitivity, and vice versa. QST unreliably detects small fiber neuropathy, potentially representing a large portion of the target population (44, 45). Therefore, it is unlikely that it will remain a standalone inclusion criterion, however, will still be collected for downstream analysis. Finally, prospective participants who are pregnant, <18 years of age, already following a WFPBD (including vegetarian and vegan diets), and those experiencing neuropathy due to other significant causes alone, will be excluded (Table 1). Leprosy patients who fulfill inclusion criteria experiencing a biochemical diabetes due to corticosteroid therapy will remain eligible for inclusion and will be considered in downstream analysis (23–28). No restriction on language will be implemented as translation services will be made available across study centres.

**Table 1 tab1:** Inclusion and exclusion criteria.

Inclusion	Exclusion
Presence of leprosy	Pregnancy
Clinical compatibility:	<18 years old
Thickened peripheral nerve	Already following a whole food plant-based diet
Presence of skin lesions	
Laboratory confirmation:	Experiencing neuropathy due to other significant underlying causes^†^
Positive slit skin smears	

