#### 2.5.2. Consent, randomization, and blinding

Patients with a history of leprosy will be pre-screened for inclusion via clinical records prior to routine follow up. Study personnel will approach eligible patients experiencing active or treated (“cured”) leprosy, as well as subjective neuropathic pain at participating tropical disease institutions. Eligible participants will receive a comprehensive in-person review of the trial protocol, including data collection requirements, and will be given the patient consent form. Patients will voluntarily confirm willingness to participate and will be free to withdraw at any point. Upon consent to enrolment, participants will be randomized to either the WFPBD intervention group, or standard of care control group. To ensure equal distribution and matching between study groups, randomization will be carried out using a stratified block method (52). Participants will be assigned to strata primarily by study site, followed by sex (male/female), and lastly age-band (18–65, >65) (Figure 2). Random sequence generation will be carried out using a computer-generated allocation sequence. Study investigators, physicians, and participants will not be blinded to group allocation due to the transparent nature of the dietary intervention and counseling. However, primary end points will be collected by independent study personnel, blinded to group allocation, allowing for a single-blinded protocol.

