### 2.6. Statistical analysis

#### 2.6.1. Sample size calculation

This is a novel RCT addressing the implications of a WFPBD on neuropathic outcomes in individuals with leprosy. This relationship has not been directly assessed in the current body of literature, however similar research questions have been assessed in individuals with diabetes mellitus. As such, the sample size calculation herein will utilize this literature as a proxy. The efficacy of a WFPBD diet on neuropathy in a diabetes cohort has been reported via the Michigan Neuropathy Screening Instrument (MNSI), including both subjective (questionnaire) and objective (physical assessment) measures. The sample size calculation was based on the MNSI questionnaire measurement as explicit details pertaining to the MNSI physical assessment were not provided. Specifically, both the type of QST utilized (vibration, perception, both, etc.) and the location the test was carried out (lesion, glove, stocking, etc.) were not mentioned. Therefore, the MNSI questionnaire was preferentially chosen as a proxy. Participants receiving the intervention reported a final mean MNSI questionnaire of 5.3 ± 2.5 compared to 7.1 ± 2.8 in the control group at study end (19). Using an opensource sample size calculator with two independent study groups, continuous endpoints, an alpha of 0.5 and 80% power, a final sample size of approximately 60 participants was ascertained (53, 54). This is a conservative estimate as source literature demonstrated a statistically significant effect on outcomes with a relatively low population of 34 individuals (19). Assuming high acceptability and a 14% withdrawal and/or loss to follow-up rate based on previous literature, a final sample size of ~70 individuals, 35 per group, will be needed to adequately power this trial (19, 47, 55, 56).

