### 3.3. Secondary outcomes

#### 3.3.1. Anthropometrics, sleep quality, physical activity, and diabetes control

As a dietary lifestyle intervention can have a drastic effect on anthropometrics, height and weight will be measured at both baseline and at the end of the study and will be used to calculate body mass index (BMI) (Figure 3). Likewise, sleep quality has been associated with neuropathy severity, and must be monitored throughout the trial. The Pittsburgh Sleep Quality index is a validated questionnaire, widely used to assess sleep perturbation due to various etiologies. Participants can be assigned a maximum of 21 points indicating severe difficulties in all areas of sleep quality (67). The PSQI will be collected at baseline and at the end of the study. Self-reported physical activity will also be collected at such intervals using the International Physical Activity Questionnaire. The IPAQ includes 27-items designed to gauge the frequency and intensity of physical activity carried out in a 7-day period, encompassing occupational, transportation, housework, and leisure activities. It has been extensively tested and validated throughout 12 countries and has previously been utilized in assessing self-reported physical activity in both diabetes and leprosy cohorts (68–70). To avoid the potentially confounding effects of additional lifestyle levers, such as sleep quality and exercise, these assessments are paramount during downstream analysis. Lastly, in individuals experiencing a biochemical diabetes due to leprosy related corticosteroids, an assessment of diabetes control including duration of illness, therapeutics used, and insulin status will also be carried out to monitor any changes throughout the trial (Figure 3). Standard biochemistry, including serum cholesterol, triglycerides, hemoglobin-A1c, serum glucose, hepatic transaminases, creatinine, and basic micronutrient panel (e.g., serum ferritin, B12) will be taken to measure diabetes parameters and general physiological status. To better ascertain the relationship between the dietary lifestyle intervention and leprosy itself, neuropathy and neuropathic pain outcomes will be stratified by secondary outputs, with specific emphasis on diabetes status, and steroid use.

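### The between-arm t-test for the continuous scores ignores the randomisation strata, baseline corticosteroid use and leprosy status; a linear model with items already collected would include them, and 'matched' should read 'stratified'

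*Protocol article*

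**What the plan says.** The Abstract (Methods) states: "Participants will be 70 age and sex-matched individuals experiencing active or treated". Section 2.5.2 gives the actual mechanism: "To ensure equal distribution and matching between study groups, randomization will be carried out using a stratified block method". It continues: "Participants will be assigned to strata primarily by study site, followed by sex (male/female), and lastly age-band", with two bands, 18–65 and over 65. No pair or individual matching is described. Section 2.6.1 sets the size: "a final sample size of ~70 individuals, 35 per group, will be needed to adequately power this trial".

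The population is mixed. Section 2.3 says the trial "will include patients experiencing active, or treated" disease. On steroids, the Introduction says "up to 65% of patients require corticosteroid treatment following reactions, resulting in steroid-induced hyperglycemia in up to 47% of individuals" who were previously glucose tolerant. It adds that poorly controlled glucose and lipids appear to worsen neuropathic pain. Section 3.3.1 states that "neuropathy and neuropathic pain outcomes will be stratified by secondary outputs, with specific emphasis on diabetes status, and steroid use".

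For analysis, section 2.6.2 names Student's t-test for between-arm comparisons of continuous variables. Leprosy classification, reactions and corticosteroid use are reported by arm. One adjusted model is planned, a logistic regression. Its example covariates include age, sex, physical activity, comorbidities and diabetes status, but not corticosteroid use, leprosy status or (by name) site.

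**The concern.** Design and analysis are not joined up. The plan stratifies on three factors and then tests the continuous scores as if it had not. If those factors relate to the score, an unadjusted test after stratified randomisation uses a standard error that is too large, and the gain from stratifying is lost.

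Steroid use, which the article itself places on a route to the outcome (steroids to glucose, glucose to neuropathic pain), is neither a stratum nor a named covariate. The logistic model does not fill the gap, because the efficacy scores are continuous and would have to be cut into two classes to enter it. Reporting results within steroid or diabetes subgroups does not adjust the overall comparison either. If the arms happen to differ in steroid use, the reader has only a by-arm table and no planned adjusted estimate.

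Separately, 'matched' claims a property the design lacks: a 20-year-old and a 64-year-old fall in the same age stratum.

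**Working it through.** **Inputs.** From section 2.6.1: MNSI questionnaire means 5.3 and 7.1 (difference 1.8), SDs 2.5 and 2.8, 80% power, about 60 evaluable, 14% loss, 35 per arm. Alpha is printed as 0.5; I read it as 0.05. Not given: the prevalence of steroid use or active disease at enrolment, and the effect of either on the MNSI.

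**The plan's own figure.** n per arm = 2(z_α + z_β)² SD²/1.8².
- Two-sided 0.05, SD 2.5: 30.3, so 31 per arm, 62 in total.
- One-sided 0.05, SD 2.8: 29.9, so 30 per arm, 60 in total.
- Loss: 60/(1 − 0.14) = 69.8, so 70.

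The stated 60 and 70 are reproduced to within rounding. Nothing in this point changes the 70.

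**Chance imbalance.** If K of 70 participants carry a factor and 35 go to each arm without regard to it, the number in one arm is hypergeometric. A gap of 20 points is 7 people (7/35).

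| Carriers K (share) | P(gap of 20 points or more) |
|---|---|
| 14 (20%) | 3.4% |
| 21 (30%) | 11.7% |
| 34 or 36 (49%, 51%) | 9.3% |
| 35 (50%) | 15.1% |
| 45 (64%) | 13.4% |
| 46 (66%) | 7.7% |

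The jumps arise because only an odd K can give a gap of exactly 7; an even K needs 8. The range is about 3–15%. For two independent factors, the chance that at least one is off by this much is 1 − (1 − 0.117)(1 − 0.077) = 18% at prevalences of 30% and 66%, and 1 − (1 − 0.151)² = 28% if both are 50%.

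**What a 20-point gap would do (assumed effect).** If the factor shifts the MNSI by d points, the arm difference moves by 0.20 × d. For d = 1, 2, 3 this is 0.2, 0.4, 0.6, or 11%, 22%, 33% of 1.8. The documents give no value for d.

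**Precision (same assumption).** Pooled SD = √((2.5² + 2.8²)/2) = 2.654. Two-sided t-test power at 30 per arm for 1.8 is 73%. An unmodelled factor at prevalence 0.5 adds variance 0.25d².
- d = 1: SD 2.70, power 72%.
- d = 2: SD 2.84, power 68%.
- d = 3: SD 3.05, power 61%.

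This is an upper view of the loss, because the quoted SDs already contain some patient heterogeneity.

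**Cost of adjusting.** With 60 evaluable, the t-test has 60 − 2 = 58 residual degrees of freedom. Sex, age, steroid use and leprosy status take 4, and site takes one fewer than the number of sites. That leaves 53 with 2 sites and 50 with 5 sites.

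**Cost of stratifying instead.** Site, sex and age-band give 8 cells with 2 sites (8.8 participants each). Adding two yes/no factors gives 32 cells (2.2 each). With 5 sites, 20 cells become 80 (0.9 each).

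**The case against.** The best defence is that nothing here is invalid. Site, sex and age are defensible strata for 70 people. Randomisation covers chance imbalance in everything else, and the test keeps its nominal error rate over repeated trials. Site may balance part of the case mix. The covariate list is open-ended, steroid use and leprosy class are shown by arm, subgroup analyses are planned, and exact model terms are often left to an analysis plan that is not shown.

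Most of this stands. It disposes of several stronger readings that a reader might infer:
- **That the trial is biased, or its false-positive rate inflated.** An inflated rate appears only if one conditions on an imbalance having occurred.
- **That active and treated patients are known to differ in the course of neuropathy.** No section says so. The Abstract describes neuropathy progressing despite effective treatment, and the Introduction says reactions occur before, during and after MDT.
- **That 65% of participants will be on steroids.** The figure concerns need for steroids following reactions, not use at enrolment.
- **That the age-band must give way to steroid use as a stratum.** That is a trade-off, not a correction.

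What the defence does not answer is that section 2.6.2 does not leave the method open. It fixes an unadjusted t-test for these scores and reserves adjustment for a logistic model.

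**Conclusion.** The point holds as a mismatch between randomisation and analysis, plus a wording error. The main comparison of continuous scores omits the randomisation strata and a factor that the article itself links, through glucose, to neuropathic pain. The case for steroid use rests on the article's text; leprosy status is included because the population is mixed by design, not because the article shows that it is prognostic.

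The size is moderate and uncertain. The 3–15% chance of a 20-point gap follows from 35 per arm over assumed prevalences of 20% to about 65%. The 0.2–0.6 point shift and the fall in power from 73% to 72–61% rest wholly on an assumed effect of 1–3 MNSI points; at 1 point the loss of power is trivial. The reason to act is that adjustment is nearly free, not that the unadjusted result would be wrong.

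**What to change.** 1. In section 2.6.2, replace the between-arm t-test for the continuous efficacy scores with a linear model containing treatment arm, site, sex, age as a continuous value, baseline corticosteroid use (yes/no) and leprosy status (active/treated). All are collected or known at enrolment. The cost is 5 to 8 degrees of freedom with 2 to 5 sites, out of about 60–70 participants.
2. In the Abstract, replace the 'matched' description with 'randomised, stratified by site, sex and age-band', and drop 'matching' from section 2.5.2. This costs nothing.
3. Optional: replace the age-band stratum with baseline steroid use before the list is generated. The number of cells stays the same, but forced balance on participants over 65 is given up. Adding both steroid use and leprosy status to the present strata is not advisable, because it leaves about two or fewer participants per cell.

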### 2.2. Study objectives and hypothesis

The overall objective of this study is to demonstrate the effect of a dietary lifestyle intervention, specifically a WFPBD, on neuropathic pain variables in leprosy. It is hypothesized that patients may demonstrate a statistically significant improvement in sensory and motor neuropathy, as well as pain, on comprehensive questionnaires and objective QST and muscle testing both within and between groups at study end. Secondary objectives include contextualizing the significance of diet in the treatment of chronic leprosy sequelae by demonstrating high tolerability and a limited side effect profile alongside aforementioned improvements in neuropathic pain. It is hypothesized that a WFPBD has the potential to serve as a low-risk, low-cost, low-tech intervention for chronic neuropathic pain, improving function and reducing overall morbidity of leprosy.

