#### 2.6.2. Continuous and categorical variables

Descriptive statistics including reported means ± standard deviation for continuous variables [questionnaires including MNSI-physical assessment, Neuropathy Total Symptom Score (NTSS), modified Medical Research Council Scale (mMRCS), Neuropathic Pain Symptom Inventory (NPSI), McGill Pain Questionnaire (MPQ), Pittsburgh Sleep Quality Index (PSQI), and International Physical Activity Questionnaire (IPAQ) summative scores, visual analog scale (VAS), anthropometrics, diabetes duration, hemoglobin A1c, and serum micronutrient levels] and proportions for categorical variables [number of adverse events, dietary adherence, insulin use, leprosy clinical status (according to the WHO and Ridley Jopling classification systems), frequency and prevalence of inflammatory leprosy reactions, corticosteroid use] will be reported by each study group (57). Between- and within-group comparisons will also be made for continuous variables using the Student’s *t*-test with reported *p*-values, and for categorical variables using the chi square or Fisher’s exact tests, reporting *p*-values with odds ratios and 95% confidence intervals. Statistics will also be reported for all time points including baseline, and end of study. Multivariate logistic regression adjusting for covariates [such as age, sex, PROGRESS+ factors (58, 59), level of physical activity, smoking status, alcohol consumption, comorbidities, diabetes status] and potential effect modifiers (such as change in weight over time, medication de-escalation over time) will be carried out to ascertain the impact of a WFPBD on PNP in leprosy patient sub-populations and under various conditions. All statistical analysis will be carried out using GraphPad Prism 8 (GraphPad, United States).

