### 3.2. Primary outcomes

#### 3.2.1. Michigan neuropathy screening instrument

The MNSI is a robust assessment of neuropathy identifiers that includes both a subjective questionnaire and objective measurements of perception via QST. Specifically, Semmes-Weinstein monofilaments will be used to measure sensation at the ulnar nerve-innervated dorsum of the hand bilaterally, given this site’s predilection for leprosy associated nerve damage, while a 128 Hz tuning fork will be utilized to test for vibration perception thresholds at the great toe (43, 60). This screening instrument has been widely used and validated in both diabetes and leprosy related neuropathy cohorts (19, 60). Scoring is based on a binomial yes/no response to specific questions where yes = 1 point and no = 0 points. Additionally, any abnormal QST result = 1 point, and a score of 4 or greater indicates the presence of neuropathy (60). The MNSI will be conducted at both baseline and at study end and will be utilized as one of the measurements for sensory neuropathy (Figure 3).

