#### 3.2.2. Neuropathy total symptom score

The Neuropathy Total Symptom Score will also be used to formulate a more robust assessment of sensory neuropathy. Unlike the MNSI, the NTSS includes considerations for both neuropathy intensity and frequency. Based on a summative questionnaire, participants can be assigned a maximum of 21.96 points, indicating greater morbidity, and depicted as a matrix comparing neuropathy intensity (mild, moderate, severe) versus frequency (occasional, often, continuous) (61). This questionnaire has been widely used and validated in cohorts of individuals with diabetes, a common comorbidity of leprosy, and will strengthen the assessment of sensory neuropathy within this trial (23, 61). The NTSS will be carried out at both baseline and study end (Figure 3).

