#### 3.2.3. Modified medical research council scale

The modified Medical Research Council Scale is a reliable tool that has been commonly used to measure motor neuropathy in patients with leprosy (43). The mMRCS utilizes voluntary muscle testing (VMT) in the assessment of motor nerve function including the facial, ulnar, median, radial, and later popliteal nerves. Patients can be assigned a maximum of 5 points, which may be downgraded by any significant reduction of VMT. A score of less than 5 is indicative of decreased motor nerve function (43). The mMRCS will be utilized at baseline and at the end of study to provide a robust assessment of motor neuropathy in this trial (Figure 3).

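### Six efficacy instruments and a safety item are all labelled primary, nothing says which of them decides the trial, and the sample size rests on one questionnaire alone

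*Protocol article*

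**What the plan says.** The abstract gives a composite list with no lead outcome: "Primary outcome measures include efficacy via visual analog scale, subjective questionnaire and objective quantitative sensory testing, as well as safety, tolerability, and harms".

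The part of section 3 headed "3.2. Primary outcomes" has seven subsections before the secondary outcomes begin:
- 3.2.1 MNSI, which "includes both a subjective questionnaire and objective measurements of perception via QST"
- "3.2.2. Neuropathy total symptom score"
- "3.2.3. Modified medical research council scale"
- 3.2.4 NPSI
- 3.2.5 MPQ
- 3.2.6 VAS
- 3.2.7 safety, tolerability, harms and adherence

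On testing, section 2.6.2 says: "Between- and within-group comparisons will also be made for continuous variables using the" Student's t-test with p-values. Categorical variables, among them adverse events and adherence, get chi-square or Fisher tests. No comparison is singled out.

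On sizing, section 2.6.1 says: "The sample size calculation was based on the MNSI questionnaire measurement".

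On objectives, section 2.2 puts tolerability in the second tier: "Secondary objectives include contextualizing the significance of diet in the treatment of chronic leprosy sequelae by demonstrating high tolerability". The same section hypothesises improvement in sensory neuropathy, motor neuropathy and pain, both within and between groups. It does not say whether one, several or all of these must be shown.

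**The concern.** A protocol has to say which comparison decides the trial. Here six scales share the primary label and the document does not rank them. A null MNSI with a significant VAS would have no agreed reading, and neither would the reverse.

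The conflict is more than formal. The overall objective concerns neuropathic pain, while the one outcome used for sizing is a neuropathy score that section 3.2.1 assigns to sensory neuropathy. The power statement therefore covers one of six primaries, and not one of the pain scales. The list of continuous variables in section 2.6.2 names the MNSI physical assessment but not the MNSI questionnaire, so the powered outcome has no visible priority in the analysis text either.

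If a single favourable scale could be presented as the primary result, the false-positive rate would be well above the nominal level. Participants are unblinded (section 2.5.2) and much of the primary set is self-reported, so a clear rule matters more.

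**Working it through.** **Inputs from the protocol.** Six efficacy instruments (3.2.1 to 3.2.6). MNSI questionnaire at study end 5.3 ± 2.5 versus 7.1 ± 2.8, so a difference of 1.8. Power 80%, about 60 participants, 14% withdrawal, about 70 in total (2.6.1). The printed alpha is 0.5.

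**Assumptions, not in the protocol.** Common pairwise correlation ρ between the six test statistics, 0 to 0.8. Success rule: both any-of and all-of are examined.

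**1. The plan's own figure, and which alpha it implies.** Per arm, n = 2 × [SD × (z_alpha + z_power) / difference]².
- Two-sided 0.05, SD 2.5: 2 × [2.5 × (1.960 + 0.842) / 1.8]² = 30.28, so 31 per arm and 62 in total, close to the stated 60.
- Two-sided 0.5, SD 2.5: 2 × [2.5 × (0.674 + 0.842) / 1.8]² = 8.87, so 9 per arm and 18 in total. Across the SD choices 2.5 to 2.8, alpha 0.5 gives 18 to 24 two-sided and 6 to 8 one-sided.
- Withdrawal: 60 / (1 − 0.14) = 69.8, so 70.

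The printed 0.5 cannot give 60, so 0.05 is used below. The match to 60 depends on the SD and sidedness chosen: the pooled SD of 2.654, two-sided, gives 70 before withdrawal. The present point does not rest on that.

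**2. Any-of rule, six between-group tests at two-sided 0.05.** With independence, the chance of at least one false positive is 1 − 0.95⁶ = 0.2649. Counting only results that favour the diet, it is 1 − 0.975⁶ = 0.141. For equally correlated normal statistics, with c = 1.96:

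1 − ∫ φ(u) {Φ[(c − √ρ u)/√(1 − ρ)] − Φ[(−c − √ρ u)/√(1 − ρ)]}⁶ du

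The diet-favouring version drops the second Φ term.

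| ρ | at least one false positive | favouring the diet |
|---|---|---|
| 0 | 26.5% | 14.1% |
| 0.3 | 24.1% | 12.2% |
| 0.5 | 20.7% | 10.4% |
| 0.7 | 16.4% | 8.2% |
| 0.8 | 13.9% | 6.9% |
| one named primary | 5% | 2.5% |

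**3. All-of rule.** The chance that all six are falsely significant cannot exceed 5%, so error is not inflated. Power is what suffers. Even if every scale had 80% power, which the protocol claims for one only, joint power would be 0.8⁶ = 26% with independence and would reach 80% only with perfect correlation.

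**4. Keeping six co-primaries with Bonferroni.** Alpha per test is 0.05 / 6 = 0.00833. Using the MNSI effect:
- SD 2.5: 47 per arm, 94 in total; 94 / 0.86 = 109.3, so 110 with withdrawal. Power at 30 per arm is about 56%.
- Pooled SD: 53 per arm, 106 in total; 106 / 0.86 = 123.3, so 124 with withdrawal. Power at 30 per arm is about 50%.

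**5. Standing of tolerability.** Primary in the abstract and in 3.2.7; part of a secondary objective in 2.2. The passages cannot all stand.

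**The case against.** **A multiplicity procedure may be in an analysis plan that is not shown.** This stands: the absence of Holm, Bonferroni or a testing order from the article is not the defect. Which outcome is primary, however, is a protocol decision, and this article does make it, by placing seven headings under that label.

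**The hypothesis in section 2.2 can be read jointly.** This also stands. The wording links sensory, motor and pain improvement, and on an all-of reading type I error is not inflated. A reader might infer that the trial has a false-positive rate of 16 to 30% instead of 5%. The document does not support that as a plain fact, for four reasons:
- It states no any-of rule and gives no correlations.
- The 30% end needs seven independent tests. That means splitting the MNSI into two, although section 2.6.2 names only its physical part. It also means treating NPSI, MPQ and VAS as unrelated although all three measure pain.
- The 16% end is only where a correlation of 0.7 falls; at 0.8, six tests give 13.9%.
- Two-sided figures count false results against the diet as well, and those would not make a positive trial.

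**Not every primary item is clearly tested.** This is fair. Adverse events and adherence are among the tested variables, but drop-out, the tolerability measure, is not listed there, and 3.2.7 speaks of summarising. The figures above therefore use the six efficacy instruments only. The within-group tests would add further chances of error, but these are not quantified here.

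**The MNSI questionnaire is not the obvious lead outcome.** This is fair too. Section 2.6.1 chose it as a proxy, and the objective concerns pain. The choice belongs to the sponsor.

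**Conclusion.** The point holds as a defect in how the protocol fixes its primary outcome. Six efficacy instruments and a safety item are called primary, no outcome or success rule decides the trial, the sample size and 80% power belong to the MNSI questionnaire alone, and tolerability is placed in two different tiers. None of this depends on an assumption.

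The numerical consequence is conditional. The any-of range in the working requires an unstated success rule, 0.05 in place of the printed 0.5, and an assumed correlation of 0 to 0.8. Within those conditions the inflation is roughly three- to fivefold (13.9 / 5 = 2.8; 26.5 / 5 = 5.3), and similar when only diet-favouring errors are counted. Under an all-of rule the harm moves from error to power. On neither reading does the stated design support the claim it would be used to make. The matter should be settled before registration, because choosing the deciding outcome after data are seen would not be credible.

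**What to change.** Before registration:
- Name one primary efficacy outcome, compared between groups at week 24. The MNSI questionnaire keeps the existing sample size basis. If the sponsor prefers a pain scale because the objective is neuropathic pain, redo the sample size for that scale.
- Make the other scales, including the MNSI physical assessment unless it is the one chosen, secondary, tested in a fixed order or with Holm adjustment.
- Treat within-group comparisons as descriptive.
- Make safety and tolerability secondary in the abstract and section 3.2.7, to agree with section 2.2.
- Correct the printed alpha in section 2.6.1.

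With the MNSI questionnaire this is a change of wording: no new data, the planned 60 and 70 keep their basis, and the primary claim is held at 5%. The price is that the remaining scales lose the primary label. Retaining all six as primaries with Bonferroni is possible, but on the MNSI effect it needs about 110 to 124 participants instead of 70, and the other five scales would still need sizing of their own.
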